**4. Responsibility of trial**

Investigator-initiated trial

**5. Address of sponsorship**

None

**6. Study period**

14 months after the approval of IRB

**7. Subjects of study**

who are scheduled for elective surgery under general anesthesia with orotracheal intubation

**8. Necessity of Study and Overview**

8.1 Background

In clinical field, water is commonly used for lubrication of tracheal tubes before tracheal intubation. Because its known lubricating properties, many clinicians expect the water can decrease airway injuries caused by intubation. However, this conventional pretreatment seems to have been performed without any validation for its advantage.

Besides, the wet condition of the tube may trigger the proliferation of respiratory pathogens, thereby increasing the risk of respiratory infection. Moreover, any external treatment applied to the tracheal tube before intubation can lead to contamination of the tube as opposed to keeping the tube inside the sterile packing.

8.2 Hypothesis and objectives

Therefore, we would conduct this study to investigate whether no pretreatment of tracheal tubes does not increase post-intubation airway-related complications as compared with water lubrication of tubes in patients undergoing general anesthesia. Our hypothesis is that a tube lubricated with water does not reduce sore throat after tracheal intubation compared to a tube without lubrication

**9. Study materials**

Klenzo 1000 mL (sodium chloride 9g, JW medical™, Korea)

**10. Inclusion and exclusion criteria**

10.1 Inclusion criteria

Participants with American Society of Anesthesiologists physical status 1–3 and aged 20–80 years, who are scheduled for elective surgery under general anesthesia with orotracheal intubation

10.2 Exclusion criteria

- Symptoms of sore throat, hoarseness, and respiratory infections as assessed by a study

investigator at baseline

- Gastroesophageal reflux diseases defined by history taking from patients

- Congenital or acquired abnormalities of the upper airway

- Previous airway surgeries

- Previous history of aspiration

- Coagulation disorders

- History of difficult intubation or conditions with an expected difficult airway including Mallampati classification ≥3 or a thyromental distance <6.5 cm

- Use of airway instruments other than a direct laryngoscope such as a fiberoptic bronchoscope,

video laryngoscope, or lighted stylet

- Anticipated nasotracheal intubation or insertion of a nasogastric tube

10.3 Sample size calculation

The primary outcome of this trial is the incidence of postoperative sore throat within 24 h after surgery. Assuming the incidence of 57% in a previous study, 135 patients are required in each group to obtain 80% statistical power, 5% risk of type-I error, and 15% noninferiority margin. The margin was determined based on our clinical judgment that the incidence of postoperative sore throat is relatively high (50–60%), so the difference within 15% in the incidence would be considered clinically noninferior. Considering 10% dropout, the estimated sample size is 300 in both groups. The sample size is calculated using a PASS software (version 11.0, NCSS, Kaysville, UT, USA).

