11.2 Randomization and Blinding

Experimental group (dry group): tracheal intubation without pretreatment (n = 150)

Control group (saline group): tracheal intubation with water lubricated tube (n = 150)

After the recruitment, participants are randomly assigned to one of the two groups in a 1:1 ratio depending on whether or not the tracheal tube is lubricated with water before intubation.

A random sequence with 4 or 6 sizes of random blocks (i.e., 4-4-4-6-4-4-6-6…) is generated

with an online tool by an assistant not involved in the trial and kept within sealed opaque envelopes. When a patient is enrolled in the trial, an anesthesia nurse opens an envelope and prepares a tracheal tube with the allocated treatment.

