**12. Statistical analysis**

Both intention-to-treat and per-protocol analyses will be performed and missing data will be imputed with the last observation carried forward value. Continuous variables

will be presented as mean and standard deviation or median and interquartile range according to the Kolmogorov-Smirnov test, and categorical variables as number of patients and proportion.

The incidence of postoperative sore throat (primary outcome)

will be compared with a noninferiority analysis.The noninferiority of the nonpretreated tube over the water-lubricated tube will be accepted if the upper bound of a 95% confidence interval is below the predetermined noninferiority margin of 15%. For secondary outcomes, continuous variables will be compared with an independent t test or the Mann-Whitney U test and categorical variables with Pearson’s chi-squared test or Fisher’s exact test.

All tests are two-sided and P < 0.05 is considered statistically significant. A statistician not involved in data collection will conduct all statistical analyses using SPSS software (version 21.0, SPSS Inc., IBM, Chicago, IL, USA).

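### The sample size matches a one-sided 5% test, but noninferiority is judged on a two-sided 95% interval, so power is about 70–75%, not the stated 80%

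*Protocol*

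**What the plan says.** Protocol Section 10.3 bases the sample size on one incidence ("Assuming the incidence of 57% in a previous study") and concludes that "135 patients are required in each group to obtain 80% statistical power, 5% risk of type-I error, and 15% noninferiority margin". It does not say whether the 5% is one-sided or two-sided. The margin is an absolute difference, since "the difference within 15% in the incidence would be considered clinically noninferior". The allowance for losses follows: "Considering 10% dropout, the estimated sample size is 300 in both groups", which is 150 per group under the 1:1 allocation of Section 11.2.

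Section 12 fixes the decision rule. The untreated tube is accepted as noninferior if "the upper bound of a 95% confidence interval is below the predetermined noninferiority margin of 15" (per cent). The same section adds, without exception, that "All tests are two-sided and P < 0.05 is considered statistically significant". The protocol nowhere mentions a one-sided 95% bound, a 90% interval or a one-sided 5% test.

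**The concern.** A noninferiority conclusion uses one limit of the interval. If the interval is a two-sided 95% interval, the chance of wrongly passing at the margin is 2.5%, so the sample size must be computed with z = 1.960. If the sample size was computed with z = 1.645, the calculation and the decision rule belong to two different tests, and the stated power is that of a test the trial will not carry out.

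Two things are at stake. The first is the chance that the trial answers its primary question when the untreated tube really is no worse. The second is a conclusion that could turn on which alpha is applied: some observed differences would pass at one-sided 5% and fail at one-sided 2.5%. If this is still open when the data are seen, the choice can be made after the fact.

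**Working it through.** **Inputs.** From Section 10.3: incidence 0.57, margin 0.15, power 80% (z = 0.8416), 135 evaluable per group, 10% dropout, 300 in total. From Section 12: upper limit of a 95% interval, all tests two-sided. Assumption: only one incidence is given, so it is taken for both groups, with a true difference of zero.

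**Step 1: reproduce the plan's figure.** With the unpooled normal approximation,

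n per group = (z_α + 0.8416)² × 2 × 0.57 × 0.43 / 0.15² = (z_α + 0.8416)² × 0.4902 / 0.0225.

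- One-sided 5% (z = 1.645): n = 134.7, rounded up to **135**, as stated. Then 135 / 0.9 = 150 per group and 300 in total, also as stated. The dropout inflation is correct.
- One-sided 2.5% (z = 1.960): n = 171.0009, strictly rounded up to **172**.

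**Step 2: could another formula give 135 at one-sided 2.5%?** Taking the variance at the null rates, or pooled, with the second group at 72% or 42%, gives 160 to 173. A continuity correction gives about 184. None comes near 135.

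**Step 3: power of the planned trial.** Power = Φ(0.15 / √(0.4902 / n) − z_α). The standard error is 0.0603 at n = 135 and 0.0572 at n = 150, so the first term is 2.489 and 2.624.

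| Evaluable per group | One-sided 5% | One-sided 2.5% (two-sided 95% interval) |
|---|---|---|
| 135 | 80.1% | **70.2%** |
| 150 | 83.6% | **74.7%** |

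**Step 4: does this depend on the approximation or on 57%?** Exact binomial enumeration at one-sided 2.5% gives:

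| Limit | n = 135 | n = 150 |
|---|---|---|
| Wald | 71.0% | 74.1% |
| Newcombe | 71.1% | 75.8% |
| Farrington–Manning | 71.0% | 74.6% |
| Wald with continuity correction | 66.7% | 70.3% |

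With a common incidence between 50% and 60%, the range Section 10.3 itself mentions, the normal-approximation power is 69.3% to 71.1% at 135 and 73.8% to 75.5% at 150. No method and no incidence in that range reaches 80%, even with no dropout.

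**Step 5: how far the two rules differ in practice.** With the standard errors of Step 3, the largest observed excess that still passes is 0.15 − z_α × SE.

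- n = 135: 3.2 percentage points at one-sided 2.5%, 5.1 at one-sided 5%.
- n = 150: 3.8 and 5.6 percentage points.

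An observed excess of, say, 4.5 points would be noninferior under one rule and not under the other.

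**The case against.** The strongest counter-argument is that the contradiction depends on reading the 95% interval as two-sided. Section 12 uses only the upper bound and does not itself call the interval two-sided. A one-sided 95% upper bound would agree with Section 10.3 and leave 80% power intact. The sentence on two-sided tests comes directly after the secondary outcomes and speaks of P values, whereas noninferiority is decided by a bound. This reading is possible but weak: a 95% confidence interval without qualification is ordinarily two-sided, and the two-sided statement covers all tests. If it was nevertheless intended, Section 12 still has to be corrected.

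Several further points stand, and they limit the claim:

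- The one-sided 5% is inferred, since Section 10.3 gives no sidedness. The inference rests on the exact match at 135 and on no standard variant matching at 2.5%.
- The written rule is stricter than the calculation. False claims of noninferiority do not become more likely, and the estimate, the interval and the margin are unaffected.
- The two power figures belong to different situations. About 70% applies if the full 10% is lost and 135 per group are analysed. About 75% applies if an intention-to-treat analysis with imputation keeps all 150.
- Power depends on the true difference being zero. By the same approximation at one-sided 2.5%, a rate of 55% with the dry tube against 57% would give 80% (n = 135) and 84% (n = 150), and a rate of 59% would give 58% and 63%. The plan does not state a benefit of the dry tube as its planning assumption, so this does not rescue the stated 80%.

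**Conclusion.** The concern holds. Sections 10.3 and 12 use different type I errors for the same primary comparison. Under the decision rule as written, the trial has about 70% power with 135 evaluable per group and about 75% with 150, where 80% is stated. The risk of failing to show true noninferiority is 25–30% instead of 20%. This rests on 57% incidence in both groups, a true difference of zero, and the ordinary two-sided reading of the 95% interval. It is a conflict between two statements in the protocol, not a detail left for a later analysis plan, and it needs to be settled before the data are analysed.

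**What to change.** Make the two sections use one alpha, fixed before any outcome data by group are seen.

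- **Keep the two-sided 95% interval (preferred, no extra patients).** State in Section 12 that the interval is two-sided, so that the noninferiority test is at one-sided 2.5%. Restate Section 10.3 as one-sided type I error 2.5%, with power of about 70% for 135 evaluable per group and about 75% for 150 per group. The cost is rewording and a less favourable stated power.
- **If one-sided 5% was intended.** State it in Section 10.3. In Section 12, say that the bound is a one-sided 95% bound, equal to the upper limit of a two-sided 90% interval, and exempt the primary test from the two-sided statement. The sample size and the 80% then stand. The cost is rewording and a more lenient test.
- **If 80% power with the two-sided 95% interval is wanted.** This needs 172 evaluable per group. With 10% dropout, 172 / 0.9 = 191.1, so 192 per group and 384 in total, which is 84 more than planned.

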10.4 How to recruit

Potential participants who meet the inclusion/exclusion criteria (See 10.1 and 10.2) are recruited at outpatient clinics or on the preoperative visit before surgery, and written informed consents are obtained from all of the participants.

**11. Study protocols**

11.1 Interventions

After overnight fasting, participants enter the operating room without any premedication and standard monitoring (electrocardiography, noninvasive arterial blood pressure, and pulse oximetry) are applied. According to random allocation, a disposable tracheal tube (Unomedical, Kedah, Malaysia), which is made of polyvinyl chloride and has a cuff with high-volume and low-pressure characteristics, is pretreated by an anesthesia nurse unaware of the study protocol. Until

tracheal intubation, the tube is placed in a 1-L bottle of sterile saline for the experimental group or kept inside the sterile packing for the control group. Tubes with 7.0-mm and 7.5-mm internal diameters are used for women and men, respectively

General anesthesia is induced with intravenous administration of propofol 1.5–2.0 mg/kg and fentanyl 1 mcg/kg. Rocuronium 0.6–0.8 mg/kg is administered for the neuromuscular blockade and train of-four counts are checked at the adductor pollicis muscle using acceleromyography (TOF-watch®, Organon Ltd., Dublin, Ireland). At a train-of-four count of 0, the tracheal tube, pretreated according to the randomization, is handed to an investigator who has a 10-year experience in tracheal intubation. The investigator performs tracheal intubation via direct laryngoscopy using either Macintosh 3 or 4 blades and evaluates the Cormack-lehane grade.

I: no difficulty

II: only posterior extremity of the glottis visible

III: only the epiglottis visible

IV: no recognizable structures visible without laryngeal manipulation

The intubation practitioner subjectively evaluates the resistance during advancement of the tube through the glottis using a four-point scale (none, mild, moderate, and severe). Intubation time, defined as the duration between the insertion of the laryngoscopic blade into the mouth and the inflation of the endotracheal tube cuff, is measured. If intubation fails, the tube tip is flexed to make a hockey-stick shape by inserting the stylet inside the tube, and then intubation is reattempted. When intubation fails in 3 attempts even using the stylet, other devices such, as a video laryngoscope, fiberoptic bronchoscope, or lighted stylet, are applied. Intracuff pressure is maintained at 25 cmH_2_O. Anesthesia is maintained with 1.0–1.5 minimum alveolar

concentration of desflurane to obtain a bispectral index (A2000 XP, Aspect Medical Systems, Newton, MA, USA) value of less than 60, and total fresh gas flow is supplied at 2 L/min throughout the operation.

At the end of surgery, reversal agents are administered to antagonize the neuromuscular blockade. After gently suctioning the oral secretions from the oropharynx, extubation is carefully performed at a train-of-four ratio above 90% when the participants are able to achieve spontaneous breathing and obey verbal commands. Extubation time is defined as the interval from cessation of anesthesia until extubation. After extubation, the presence of blood on the tube surface or in the oral cavity is examined. An investigator blinded to the group assignment evaluates patient-reported sore throat at 0, 2, 4, and 24 h after surgery.

[figure not shown]

The investigator also examines oropharyngeal injuries via direct inspection using a penlight and tongue depressor with regard to the location (posterior pharyngeal wall, uvula, tonsillar fossa, pillar, or others) and type (hyperemia, edema, hematoma, or others) at 2 and 24 h after surgery. The amount of intraoperative and postoperative analgesic drugs is checked until 24 h after surgery.

At 7 days after surgery, the investigator also asks about the symptoms of respiratory infections, such as cough, sputum, rhinorrhea, sore throat, or fever, and whether the patients have been diagnosed with a common cold, tonsillitis, pneumonia, or any other respiratory infectious diseases and prescribed related medications postoperatively. If the patients have been discharged from hospital, they are contacted by telephone and asked about respiratory infections.

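### Protocol Section 11.1 assigns the saline-soaked tube to the experimental group and the dry tube to the control group, the reverse of the arm definitions in Section 11.2

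*Protocol*

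**What the plan says.** Four places in the protocol bear on which arm is which.

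- Section 11.1 (Interventions) describes tube preparation before intubation: "placed in a 1-L bottle of sterile saline for the experimental group or kept inside the sterile packing for the control group".
- Section 11.2 (Randomization and Blinding) defines the randomised arms: "Experimental group (dry group): tracheal intubation without pretreatment (n = 150") and "Control group (saline group): tracheal intubation with water lubricated tube (n = 150").
- Section 8.2 (Hypothesis and objectives) asks "whether no pretreatment of tracheal tubes does not increase post-intubation airway-related complications as compared with water lubrication of tubes".
- Section 12 (Statistical analysis) states the decision rule, for a margin of 15%: "The noninferiority of the nonpretreated tube over the water-lubricated tube will be accepted if the upper bound of a 95% confidence interval is below" that margin.

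On who handles the allocation, Section 11.1 says the tube "is pretreated by an anesthesia nurse unaware of the study protocol", and Section 11.2 says that "an anesthesia nurse opens an envelope and prepares a tracheal tube with the allocated treatment".

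**The concern.** The same two group labels carry opposite treatments in two operative sections, one describing how the tube is prepared and the other defining what is randomised. A noninferiority comparison runs in one direction only, so exchanging the labels does not just relabel a table. It replaces the question of whether dry is acceptably close to saline with the question of whether saline is acceptably close to dry.

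The protocol does not say whether the envelopes contain a treatment name or a group label. The tube preparation actually received is not among the variables listed in Section 11.4, and receiving the wrong tube is not among the drop-out criteria in Section 11.7. If labels were mixed up, nothing in this document would clearly bring it to light. At stake is the sign of the primary comparison.

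**Working it through.** **1. The sections side by side**

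| Section | Saline tube | Dry tube |
|---|---|---|
| 8.2 objective | reference | tested |
| 11.1 preparation | experimental | control |
| 11.2 arm definitions | control | experimental |
| 12 decision rule | reference | tested |

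Sections 11.1 and 11.2 are exact opposites. Sections 8.2 and 12 do not use the group labels at all. They name the tubes, and their roles match Section 11.2.

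**2. Direction of the written test.** Sore throat is an undesirable outcome. Section 12 accepts noninferiority of the untreated tube when an upper confidence limit lies below a positive margin. That makes sense only for incidence(dry) minus incidence(saline). The subtraction is not written out, but the rule determines it.

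**3. The plan's own sample size.** Inputs from Section 10.3: 57% in both arms, margin 0.15, power 80%, type I error 5%, dropout 10%. Taking the 5% as one-sided:

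n = (1.645 + 0.842)² × 2 × 0.57 × 0.43 / 0.15² = 134.7, so 135 per group.

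135 / 0.90 = 150 per group, 300 in total.

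Both stated figures reproduce. The calculation is symmetric in the arms (same rate, 1:1 allocation), so reconciling the labels changes neither. Whether a one-sided 5% fits the 95% interval in Section 12 is a separate question.

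**4. What a complete label reversal would do to one result.** 150 per group comes from Section 11.2 and 57% for saline from Section 10.3. The dry rate of 67% is assumed.

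SE = √[(0.67 × 0.33 + 0.57 × 0.43) / 150] = 5.57 points.

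- Correct labels: +10 ± 1.96 × 5.57 = -0.9 to +20.9. The upper limit exceeds 15, so noninferiority is not shown.
- All labels reversed: -20.9 to +0.9. The upper limit is below 15, so noninferiority is declared.

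**5. Range over assumed dry rates.** With 135 evaluable per group, saline at 57%, and d the true difference as analysed, the probability of declaring noninferiority is Φ[(0.15 − d)/SE − 1.96].

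| True dry rate (assumed) | Correct labels | All labels reversed |
|---|---|---|
| 57% | 70.2% | 70.2% |
| 62% | 38.8% | 91.8% |
| 67% | 13.4% | 98.9% |
| 72% (at the margin) | 2.5% | 99.9% |

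**6. Partial mix-up.** If a fraction f of each arm received the other tube, the expected difference by assigned arm is multiplied by (1 − 2f). A true 15-point excess becomes 9 points at f = 20%, 0 at f = 50% and -15 at f = 100%. These values of f are assumptions. Any mixing with f above zero moves the expected result towards a false claim of noninferiority.

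**The case against.** The strongest reply is that this is a drafting slip in one clause of Section 11.1. A reader might infer that the noninferiority test itself is reversed or undefined. The documents do not support that: Section 12 names the tubes rather than the groups, and with Section 8.2 it fixes the direction as dry minus saline.

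A reader might also infer that tubes will be, or have been, prepared the wrong way round. That is not shown either. Either set of definitions, used consistently from preparation to analysis with Section 12's tube-named rule, gives the right answer. Harm needs a further step: bare experimental/control labels used under one section and decoded under the other. No document shows such labels on envelopes or in a dataset. Section 11.2 tags its arms as dry and saline and has the nurse prepare the allocated treatment. A nurse who does not know the protocol would more naturally be handed a treatment name than be left to decode a label from Section 11.1.

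All of that stands, and it limits the consequence to a conditional one. It does not remove the contradiction. Both passages are current operative text, the envelope contents are not described, and a preparer unaware of the protocol is poorly placed to notice an inverted instruction.

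**Conclusion.** The contradiction between Sections 11.1 and 11.2 is real and must be corrected. It is an internal inconsistency in the definition of the arms, not a design choice. As written, the test direction can be determined and the sample size of 135 per group and 300 in total is unaffected.

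The size of the possible error depends on two assumptions: that labels are applied under one section and read under the other, and that the dry tube is truly worse. With complete reversal, a dry tube worse by the full 15 points would pass 99.9% of the time instead of 2.5%. If the two tubes have equal incidence, reversal leaves the probability of passing unchanged. The 62%, 67% and 72% dry rates are illustrations; the protocol gives only 57%.

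**What to change.** - Reconcile Sections 11.1 and 11.2 so that each group has one definition throughout the protocol.
- Identify the arms as dry and saline wherever allocation is recorded or analysed, including the envelopes, case report form and analysis dataset, so that nothing depends on decoding a group label.
- For clarity, state in Section 12 that the analysed quantity is incidence(dry) minus incidence(saline), and that noninferiority of the dry tube is accepted if the upper 95% limit is below +15 percentage points.
- If any patients have already been randomised, check the recorded tube preparation against the allocation list.

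The cost is a correction to one clause, one added sentence in Section 12 and a check of envelope and dataset coding. No sample size, endpoint or margin changes.

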11.3 Administration and dose of drug: N/A

11.4 Outcome measurements

- Demographic data: sex, age, body weight, height, body mass index

- airway related parameters: modified Mallampati class, Cormack-Lehane grade, thyromental distance

- ease of mask ventilation (easy/moderate/difficult)

- intubation time, duration, resistance of tube advancement

- hemodynamic parameter change before and after the intubation : mean blood pressure, heart rate, saturation

- Extubation time

- oral bleeding, blood tinged tracheal tube cuff, mechanical injury of tracheal tube

- Sore throat and hoarseness at 0, 2, 4 and 24 after the surgery

- Oropharyngeal injuries at 2 and 24 h after the surgery

- Amount of postoperative analgesics

- Symptoms of respiratory infections of diagnosis of any other respiratory infectious diseases up to 7 days after the surgery

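### The secondary-outcome rule ignores the order of the resistance scale and leaves the haemodynamic change unadjusted: valid tests, but less efficient than the data allow

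*Protocol*

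**What the plan says.** Protocol Section 11.1 asks the person intubating to grade "resistance during advancement of the tube through the glottis using a four-point scale (none, mild, moderate, and severe". Section 11.4 lists this resistance as an outcome. It also lists a three-level rating, "ease of mask ventilation (easy/moderate/difficult", and "hemodynamic parameter change before and after the intubation : mean blood pressure, heart rate, saturation".

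Section 12 gives one rule for all secondary outcomes. Its first half sends continuous measures to a t test or Mann-Whitney U. Its second half, on the remaining outcomes, reads "categorical variables with Pearson’s chi-squared test or Fisher’s exact test". The section adds that "All tests are two-sided and P < 0.05 is considered statistically significant". It names no test for ordered categories and no covariate adjustment, and it does not match any secondary variable to a test by name. No power is stated for any secondary outcome.

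**The concern.** A four-level graded scale falls most naturally under the categorical half of the rule. Both tests named there are blind to order: exchanging the labels of the mildest and most severe levels would leave the P value unchanged. If an untreated tube meets more resistance, the effect should run in one direction along the scale. A test that spreads its power over three degrees of freedom is then less sensitive than one aimed at that direction.

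For haemodynamics, the outcome is a change score compared between arms without adjustment. The pre-intubation value is available for every patient whose change can be computed. Using it as a covariate is at least as precise in large samples.

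Resistance is arguably the measurement closest to the mechanism of lubrication, although that is an inference and the protocol does not say so. The trial hopes to show that omitting lubrication does no harm. A non-significant result from an insensitive secondary test is easily read as support for that, so avoidable loss of sensitivity is worth removing.

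**Working it through.** **Group size.** The protocol's only sample-size figure belongs to the primary outcome. It reproduces with a one-sided 5% level: n = 2 × 0.57 × 0.43 × (1.645 + 0.842)² / 0.15² = 134.7, so 135 per group, and 135 / 0.9 = 150. There is no secondary-outcome figure to reproduce. The calculations below use 150 per group (Section 11.2) and two-sided 0.05 (Section 12).

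**Ordered scale, analytic check.** A one-degree-of-freedom test has 80% power at noncentrality (1.96 + 0.842)² = 7.85. With the same noncentrality on three degrees of freedom, as for a 2 × 4 table, power is 64%. This indicates the price of ignoring order when the shift is in one direction.

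**Ordered scale, simulation.** Level frequencies are assumed. The second arm is shifted by a proportional odds ratio (OR), which multiplies the odds of exceeding each level. Pearson's chi-squared is compared with the tie-corrected Mann-Whitney test at 150 per group.

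| Assumed split, none/mild/moderate/severe (%) | OR | Chi-squared | Rank test |
|---|---|---|---|
| 60/28/10/2 | 1.6 | 37–39% (two runs) | 54–56% |
| 60/28/10/2 | 1.8 | 59% | 76% |
| 60/28/10/2 | 2.0 | 75% | 88% |
| 70/20/8/2 | 2.0 | 70% | 84% |
| 50/30/15/5 | 2.0 | 78% | 90% |
| 40/30/20/10 | 2.0 | 80% | 91% |
| 85/10/4/1 | 2.0 | 50% | 68% |

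The gain is about 12 to 18 points. The smallest in the table is 11, where chi-squared already has 80% power. At 135 per group and OR 1.5 to 2.0 the gains are about 9 to 18 points.

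**Counter-case.** With 50/30/15/5% against 55/17/23/5%, a difference that does not run one way, chi-squared has about 67% power and the rank test about 5%.

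**Haemodynamics.** Assume one value before and one after intubation, equal variance σ² at both times, and correlation ρ. Neither σ nor ρ is in the protocol.

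- Change-score variance: 2σ²(1 − ρ)
- ANCOVA residual variance: σ²(1 − ρ²)
- Ratio: (1 − ρ²) / [2(1 − ρ)] = (1 + ρ)/2

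For an assumed difference of 0.3σ and 150 per group, power is Φ(0.3 × √75 / s − 1.96), where s² is the variance above with σ = 1.

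| ρ | Variance ratio | Change-score power | ANCOVA power |
|---|---|---|---|
| 0.3 | 0.65 | 59% | 78% |
| 0.5 | 0.75 | 74% | 85% |
| 0.7 | 0.85 | 92% | 95% |
| 0.8 | 0.90 | 98% | 99% |

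Example at ρ = 0.5: the change score gives 2.598 / 1 − 1.96 = 0.638, so 74%. ANCOVA gives 2.598 / √0.75 − 1.96 = 1.04, so 85%.

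**The case against.** The strongest reply is that nothing here is an error. The tests hold their type I error under randomisation, and matching each variable to a test, with covariates, is ordinary SAP content. Mann-Whitney U is already in the plan. This stands in part. The pairing of the resistance scale with chi-squared follows from the general rule, not from a named assignment, and a SAP not shown may settle it. But Section 12 does not leave the matter open: it fixes a rule that, as worded, sends ordered scales to order-blind tests.

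Other points that stand:

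- A reader might infer that the baseline haemodynamic value is thrown away. It is not: Section 11.4 defines the outcome as a change, which uses it, only less efficiently. At ρ of 0.7 or more the loss is small.
- A reader might infer that order-blind tests bring no benefit. The counter-case shows otherwise, although such a pattern is implausible for resistance.
- Proportional odds is close to the ideal case for a rank test, so the simulated gains are favourable ones.
- With a sparse severe level, Fisher's test may replace Pearson's. For 60/28/10/2% and OR 1.8, the second arm has 0.02/0.98 × 1.8 = 0.0367 in odds, or 3.5%. The expected count is then 150 × (0.02 + 0.035)/2 ≈ 4 per arm, so 2 of 8 cells fall below 5. Fisher's test ignores order too, but its power was not computed.
- Resistance is a subjective rating by the person handling the tube, and Section 11.1 states blinding only for the postoperative assessor. A more sensitive test does not cure rating bias.
- The same remedy could seem to apply to graded sore-throat severity, but the visible text defines only incidence as the sore-throat outcome (Section 11.5).

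**Conclusion.** The point holds as a matter of efficiency in secondary outcomes, and it is minor. Under one-directional proportional-odds shifts (OR 1.6 to 2.0, 150 per group), order-blind testing of the resistance scale costs about 12 to 18 power points. Relative to a change score, ANCOVA would cut variance by 25% at ρ = 0.5 and 15% at ρ = 0.7. The level frequencies, odds ratios, correlations, equal variances and 0.3σ effect are all assumptions.

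A reader might go further and conclude that the secondary tests are invalid or that the trial's main conclusion is at risk. The protocol supports neither. The planned tests are valid, no secondary power is claimed, and the noninferiority comparison of sore throat does not use these tests.

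**What to change.** Add two sentences to Section 12:

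1. Ordered scales, such as resistance to tube advancement, will be compared by the Mann-Whitney U test with correction for ties, or by the linear-by-linear trend test. Name one of the two in advance. Pearson's or Fisher's test then applies to unordered and two-level outcomes.
2. Post-intubation mean blood pressure and heart rate will be compared by ANCOVA, with the pre-intubation value as covariate. Saturation is left out of this proposal because values near the ceiling suit a linear model poorly.

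If a SAP exists, it should carry the same wording. The change should be made before unblinding, so that the test is not chosen after seeing the data.

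The cost is wording only: no extra patients, visits or measurements, and SPSS has these methods. The one statistical price is little power for non-monotone differences on the ordered scales. Tabulating all four resistance levels by arm would leave any such pattern visible.
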